**Methods and analysis:**

This is a prospective, single-center, double-blind, randomized, propofol-controlled, non-inferiority trial. A total of 256 patients aged 65 years or older, who are scheduled for same-day bidirectional endoscopy under sedation, will be randomly allocated, in a 1:1 ratio, to either fospropofol group or propofol group (n = 128 in each group). All patients will receive analgesic pre-treatment with sufentanil 5 μg. Two minutes later, an initial bolus dose of fospropofol 6.5 mg/kg or 1.5 mg/kg propofol and supplemental doses of fospropofol 1.6 mg/kg or 0.5 mg/kg propofol will be titrated as needed to achieve target sedation levels during the procedures. The primary outcome is the success rate of same-day bidirectional endoscopy. Secondary outcomes include the time to successful induction of sedation, duration, time to being fully alert, time to patient discharge, endoscopist satisfaction, patient satisfaction, and the top-up frequency and dosage of sedative medications. The safety endpoints consist of adverse events concerning cough reflex, gag reflexes, body movement, muscular tremor, and pain on injection. Sedation-related AEs, including episodes of desaturation, severe desaturation (SpO_2_ < 90%), hypotension, severe hypotension (decrease in MBP ≥30% of baseline), and bradycardia, will also be recorded. Data will be analyzed on an intention-to-treat basis.

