## 1 Introduction

With life expectancy rising around the world, the incidence of gastrointestinal diseases increases in parallel with the aging of population. Research statistics indicate that elderly people account for a high proportion of all newly diagnosed gastrointestinal malignancies (Hall et al., 2005). Gastrointestinal endoscopy is an effective diagnostic method for gastrointestinal diseases. Same-day bidirectional endoscopy (esophagogastroduodenoscopy and colonoscopy) has become increasingly common due to its cost-effectiveness and ability to enhance decision-making (Urquhart et al., 2009). Recent studies have shown that the optimal sequence for patients undergoing same-day bidirectional endoscopy under sedation is esophagogastroduodenoscopy followed by colonoscopy (Laoveeravat et al., 2020).

Moderate sedation is necessary during gastrointestinal endoscopy to reduce the patient’s memory of the event, make them more comfortable and less anxious, and significantly improve the procedure outcome (Early et al., 2018; Zhou et al., 2021). Though the types of medications used for sedation in elderly patients are not different from those in younger patients, it is important to be aware of the increased sensitivity of this population to sedative medications (Chandrasekhara et al., 2013). Elderly patients are at increased risk for adverse events, such as hypoxemia, hypotension, arrhythmias, and esophageal reflux during the gastrointestinal endoscopy (Laanani et al., 2019; Shimizu et al., 2021). Therefore, clinicians should pay more attention when administering sedative medications to elderly patients undergoing gastrointestinal endoscopy. Over the long term, propofol is the most commonly used sedative agent for gastrointestinal endoscopy due to its rapid onset of action and fast recovery (Zhang et al., 2018). Propofol combined with opioids has become the most common regimen of sedation in China (Zhou et al., 2021). However, due to its narrow therapeutic window, propofol poses high risks of adverse events such as respiratory depression, hypotension, and pain on injection, especially in elderly patients (Shimizu et al., 2021).

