Fospropofol disodium for injection (manufactured by Yichang Human well Pharmaceutical Co., Ltd., Hubei, P. R. China) is a novel water-soluble prodrug of propofol. It has a unique pharmacokinetic and pharmacodynamic profile compared to lipid propofol (Wu et al., 2021). As a prodrug of propofol, fospropofol’s pharmacologic activity results from its breakdown by alkaline phosphatase and subsequent release of propofol (Liu et al., 2020). Compared to propofol lipid emulsion, it exhibits a longer time to peak clinical effect and a more prolonged action, resulting in smoother hemodynamic and respiratory depression in patients (Abdelmalak et al., 2012). Additionally, it does not cause a burning sensation upon IV administration, which is a common side effect of propofol (Garnock-Jones and Scott, 2010). The available evidence suggests that fospropofol sedation is effective for patients undergoing esophagogastroscopy, colonoscopy, and flexible bronchoscopy (Cohen et al., 2010; Gan et al., 2010; Bergese et al., 2013; Wu et al., 2021). Despite these promising findings, the optimal sedation regimen for fospropofol to facilitate same-day bidirectional endoscopic procedures remains unclear. Moreover, it is worth noting that most studies have been conducted on populations with a wide age range and have not investigated the safety of fospropofol in elderly patients (Abdelmalak et al., 2012). As a result, we designed this study to evaluate the efficacy and safety of fospropofol in comparison with propofol for sedating elderly patients undergoing same-day bidirectional endoscopy.

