### 2.6 Safety assessments

Safety will be assessed by the rate of occurrence of adverse events (AEs). AEs are evaluated for frequency, severity, association to the study drug, relationship to procedure, and outcome. The severity of AEs is graded based on the Common Terminology Criteria for Adverse Events (CTCAEs, version 5.0). The causal relationship of an AE to the investigated drug (fospropofol or propofol) will be assessed by the investigator using the classifications shown in Table 2 according to previous literature (Luo et al., 2022). AEs are considered severe if they affects a patient’s daily function or threatens their life. If cough reflex, gag reflexes, body movement, muscular tremor, pain on injection, or other reactions caused by operation irritation will be observed in patients, they are recorded as operational reactions of gastrointestinal endoscopy. Sedation-related AEs, including hypoxia, hypotension, bradycardia, and prolonged sedation, are evaluated from the time of administration of bolus doses of the study drug until the discharge of patients. Hypoxia is defined as pulse oxygen saturation (SpO_2_) < 90% lasting for >30 s; hypotension is defined as systolic blood pressure (SBP) < 90 mmHg or a decrease of 20% from baseline lasting for >2 min; bradycardia is defined as heart rate (HR) < 50 beats/min and lasting for >2 min. Prolonged sedation is defined as a MOAA/S score ≤4 for more than 30 min after the end of the colonoscopy.

**TABLE 2 T2:** Classification of AEs potentially associated with fospropofol or propofol.

Indicator	Definitely related	Probably related	Possibly related	Possibly not related	Not related
Reasonable time sequence	Yes	Yes	Yes	Yes	Yes
Belongs to the type of reaction known to be produced by the study drug	Yes	Yes	Yes	No	No
Reaction may be improved after discontinuation of the study drug	Yes	Yes	Yes or No	Yes or No	Yes or No
Reaction may re-occur with medication	Yes	?	?	?	No
There is another explanation for the reaction	No	No	Yes	Yes	Yes

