### 2.10 Data management and statistical analysis

Statistical analysis in this trial will be performed using SPSS 25 (SPSS Inc., Chicago, Illinois, United States). Continuous variables are presented as the mean ± standard deviation (SD) or median with the upper and lower quartiles, whereas categorical variables are presented as frequencies and percentages. A P-value <0.05 is considered statistically significant. For the primary efficacy outcome, the difference in gastrointestinal endoscopy success rate between fospropofol and propofol groups and the corresponding two-sided 95% confidence intervals (CIs) will be calculated. Non-inferiority between fospropofol and propofol is concluded if the lower limit of the two-sided 95% CI of the difference in success rate between fospropofol and propofol groups exceeds the non-inferiority margin (−8%). The success rates of gastrointestinal endoscopy will be compared between the fospropofol and propofol groups using the Chi-square test or Fisher’s exact test. The Shapiro-Wilk’s test will be used to assess the data distribution. For comparison of secondary efficacy outcomes, the Cochran–Mantel–Haenszel (CMH) test or Fisher’s exact test will be used to compare the categorical variables between two groups, while a t-test (normal distribution) or Mann-Whitney U test (non-normal distribution) is used to compare continuous variables, as appropriate. The incidence of AEs and drug-related AEs between the two groups will be compared using a chi-square test or Fisher’s exact test. In addition, the further interaction analysis across the subgroups, including age (65–79 years vs. ≥ 80 years), history of cardiovascular, renal, hepatic, and pulmonary diseases (yes vs. no), as well as interventional therapeutic endoscopic procedures (yes vs. no), will be carried out using a logistic regression model to adjust the study outcomes for above-mentioned potential confounding factors. All randomly assigned patients who receive at least one dose of the study medication will be included in the full analysis set (FAS) according to the intention-to-treat (ITT) principle, and at least one evaluable efficacy outcome is used for the analysis of all efficacy outcomes and baseline characteristics of patients. The safety set (SS), which includes all patients based on the “as treated” principle, will be used for the analysis of safety outcomes. Since the anticipated protocol violation will be uncommon and missing data will be supposed to be missing at random, the interim analysis or imputation for missing data are not performed in this trial.

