
## 3 Discussion

Over the past decade, the volume of gastrointestinal endoscopic procedures has increased 10-fold (Xin et al., 2022; Song et al., 2023). Many patients now undergo esophagogastroduodenoscopy and colonoscopy during the same hospital visit, commonly known as same-visit bidirectional endoscopy. Same-day bidirectional endoscopy has been increasingly implemented because it reduces costs and facilitates decision-making for other interventions or treatments needed by patients (Laoveeravat et al., 2020). To improve patient comfort and facilitate these procedures, the use of sedation has been increasingly requested by patients (Dossa et al., 2021). Propofol is a sedative agent commonly used for sedation in gastrointestinal endoscopy (Grocott, 2018; Zhang et al., 2018). Although its pharmacological properties render propofol an almost ideal drug to achieve and maintain the desired level of sedation in gastrointestinal procedures (Stogiannou et al., 2018), it is not without its drawbacks, as adverse events such as respiratory depression, hypotension, and pain on injection have been reported (Sneyd et al., 2022). In previous studies of patients undergoing gastrointestinal endoscopy with propofol sedation, the incidence of desaturation and hypotension events was approximately 30% (Chiang et al., 2013; Eberl et al., 2020). In an analysis of national claims databases in France, Laanani et al. found that SAEs related to screening and diagnostic colonoscopies were more frequent in older patients, particularly those with comorbidities (Laanani et al., 2019). Furthermore, same-visit bidirectional endoscopy is a more complex and prolonged endoscopic procedure compared to a single either esophagogastroduodenoscopy or colonoscopy. Therefore, special considerations should be given for elderly patients received same-visit bidirectional endoscopy. Currently, the best sedation regimen to facilitate a same-visit bidirectional endoscopy in an effective, safe and satisfactory manner for both patient and endoscopist is still not clear (Song et al., 2023).

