Fospropofol is a water-soluble, phosphate ester prodrug, which can be metabolized by alkaline phosphatases to release liberated propofol after intravenous administration (Garnock-Jones and Scott, 2010). The released propofol from fospropofol binds to the γ-aminobutyric acid (GABA) receptor and thereby potentiates GABA-inhibitory synaptic currents to induce sedative effects (Garnock-Jones and Scott, 2010). A study of its pharmacodynamic/pharmacokinetic relationship in 12 healthy volunteers found that an intravenous bolus 10 mg/kg dose of fospropofola achieved propofol plasma maximum concentration of 2.2 mg/mLafter 8 (range 4–13) minutes, and reached the minimum mean MOAA/S score of 1.2 after 7 (1–15) minutes. Participants in this study completely recovered from sedation after 21–45 min following fospropofol administration (Bengalorkar et al., 2011). As a new sedative, fospropofol is expected to have the same sedative efficacy as propofol in elderly patients undergoing same-day bidirectional endoscopy, with a lower incidence of adverse reactions caused by hemodynamic and respiratory depression than that of propofol. On bassi of a phase II dose-response trial in patients undergoing colonoscopy, fospropofol 6.5 mg/kg was determined as the ideal dose, as no recorded episodes of deep sedation occurred during procedures under this dose (Cohen, 2008). In addition, both physicians and patients mostly preferred for fospropofol 6.5 mg/kg over the other doses (Cohen, 2008). In two clinical trials, fospropofol was shown to be safe and well tolerated at an initial dose of 6.5 mg/kg intravenously with supplemental doses as moderate sedation for elderly, obese, and high-risk patients in minor surgical procedures (Gan et al., 2010; Bergese et al., 2013). Fospropofol disodium for injection is a prodrug that is metabolized into propofol to produce a general anesthetic effect when administered intravenously. A phase 3 trial demonstrated that fospropofol disodium was not inferior to propofol for general anesthesia induction in American Society of Anesthesiologists (ASA) physical status I-II adult patients undergoing elective surgery and reduced the incidence of pain at the injection site (Wu et al., 2021). In addition, fospropofol’s slower onset should have less impact on patient’s hemodynamics compared to propfol, although it may potentially slow patient recovery (Gan et al., 2010). In clinical conditions where a more prolonged effect is desired and immediate onset of action is less important, fospropofol may have advantages over propofol. A pilot study has shown that fospropofol, administered in either an infusion/bolus or infusion-only regimen, is tolerable and effective for the short-term induction and maintenance of sedation in mechanically ventilated intensive care unit patients (Candiotti et al., 2011). These findings have prompted to exploration of fospropofol in providing sedation for elderly patients undergoing same-day bidirectional endoscopic procedures. However, the role of fospropofol sedation for same-day bidirectional endoscopy in elderly patients has not been fully determined. To our knowledge, this will be the first randomized controlled trial to assess the efficacy and safety of fospropofol sedation for same-day bidirectional endoscopy in elderly patients. In our patients, an initial bolus dose of fospropofol 6.5 mg/kg in combination with sufentanil 5 μg will be used for sedation induction, followed by supplemental doses of fospropofol 1.6 mg/kg as needed to achieve target sedation levels. This strategy will minimize the risk of oversedation and associated complications. Moreover, several confounding factors, which can influence the study outcomes, must be appropriately managed in this study to ensure that the reliable conclusions are obtaine. Subgroup analyses of the efficacy and safety assessments will be performed on basis of age, interventional therapeutic endoscopic procedures, history of cardiovascular, renal, hepatic, and pulmonary diseases.

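### Section 2.6 records pain on injection as a reaction to the endoscopy, although the protocol treats it elsewhere as a propofol adverse effect, which probably keeps it out of, or down-grades it in, the drug-related AE comparison

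*Protocol article*

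**What the plan says.** Section 2.6 (Safety assessments) lists cough, gag, body movement and muscular tremor, and continues: "pain on injection, or other reactions caused by operation irritation will be observed in patients, they are recorded as operational reactions of gastrointestinal endoscopy". A separate list follows: "Sedation-related AEs, including hypoxia, hypotension, bradycardia, and prolonged sedation, are evaluated from the time of administration of bolus doses". That list does not name injection pain.

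Other parts of the article describe the same event differently:

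- Abstract, Methods and analysis: "The safety endpoints consist of adverse events concerning cough reflex, gag reflexes, body movement, muscular tremor, and pain on injection".
- Introduction, on propofol: "propofol poses high risks of adverse events such as respiratory depression, hypotension, and pain on injection, especially in elderly patients".
- Introduction, on fospropofol: "it does not cause a burning sensation upon IV administration, which is a common side effect of propofol".
- Discussion, on propofol: "adverse events such as respiratory depression, hypotension, and pain on injection have been reported".
- Discussion, on an earlier phase 3 comparison with propofol: fospropofol "reduced the incidence of pain at the injection site".

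Section 2.10 then plans the safety comparison: "The incidence of AEs and drug-related AEs between the two groups will be compared", by a chi-square or Fisher's exact test. Table 1 has a row for injection pain, assessed during sedation.

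**The concern.** Section 2.6 is a recording rule, so it fixes how the event is classified before anyone judges its cause. By its wording, injection pain is one example of irritation from the procedure. The protocol's own account makes it an effect of one of the two study drugs, and one on which the arms are expected to differ.

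An expected drug effect that is filed under the procedure may not reach the drug-related AE count. The loss would be unequal: many events could go from the propofol arm and few from the fospropofol arm. Propofol's drug-related AE incidence would be understated, and the between-arm comparison would miss a difference that the rationale for the trial itself describes.

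**Working it through.** The document states no figure for this point, so the check is mainly a comparison of the text.

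**Step 1. Can the procedure be the cause?** Section 2.4 gives sufentanil, then the initial bolus of study drug to reach the sedation target, and only then does the endoscopist begin. Pain from that bolus comes before the scope is inserted, so irritation from the procedure cannot explain it.

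**Step 2. What would Table 2 give?** Two rows matter.

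| Table 2 row | Definitely | Probably | Possibly | Possibly not | Not |
|---|---|---|---|---|---|
| Known type of reaction for the drug | Yes | Yes | Yes | No | No |
| Another explanation exists | No | No | Yes | Yes | Yes |

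On the protocol's own account, injection pain with propofol scores Yes on the first row. If the operational label is taken as another explanation, the second row is also Yes. The only column that fits both answers is possibly related. Without the label, definitely or probably related would be open. So even if Table 2 is applied, the label caps the grade. If the label is read as replacing the drug-causality judgement, the event is not counted as drug-related at all.

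**Step 3. How far could the comparison move?** This is an illustration only, because the documents give no incidence of injection pain. Assumptions: other drug-related AEs occur in 30% of patients in both arms, pain is independent of them, there are 128 patients per arm (section 2.9), and the test is two-sided at 0.05. With pain counted, the incidence in an arm is 1 − (1 − 0.30) × (1 − pain rate). With pain left out, both arms stand at 30% and the difference is 0.

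| Assumed pain, propofol vs fospropofol | Propofol | Fospropofol | Difference | Power, pain counted among drug-related AEs | Power, pain compared alone |
|---|---|---|---|---|---|
| 10% vs 2% | 1 − 0.70 × 0.90 = 37.0% | 1 − 0.70 × 0.98 = 31.4% | 5.6 points | 15% | 77% |
| 20% vs 5% | 1 − 0.70 × 0.80 = 44.0% | 1 − 0.70 × 0.95 = 33.5% | 10.5 points | 41% | 96% |
| 40% vs 5% | 1 − 0.70 × 0.60 = 58.0% | 33.5% | 24.5 points | 98% | near 100% |
| 60% vs 5% | 1 − 0.70 × 0.40 = 72.0% | 33.5% | 38.5 points | near 100% | near 100% |

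**Step 4. Patients, not events.** At an assumed 10% to 40% with propofol, 128 × 0.10 = 13 to 128 × 0.40 = 51 propofol patients would have injection pain. Section 2.10 compares incidence, and some of these patients would already count through another drug-related AE. Under the 30% assumption the net change is 128 × 0.70 × 0.10 = 9 to 128 × 0.70 × 0.40 = 36 patients.

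**The case against.** The strongest reply is that the exclusion is an inference. Section 2.6 says that AEs are evaluated both for association with the drug and for relationship to the procedure, so a procedural label need not rule out a drug attribution. Nothing says that an operational reaction is not an AE, and the Abstract calls these same items adverse events. A reader might infer that injection pain is never graded by Table 2 and is certainly omitted from section 2.10. The documents do not support that certainty. The passages conflict, and omission or down-grading is the likely result of following section 2.6 as written.

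A reader might also infer that the benefit disappears from the results. It does not: injection pain is a named safety endpoint with its own row in Table 1, and it can be compared by arm whatever its label. Step 3 shows that a separate comparison has more power than the pooled one in the first three scenarios. Nor can the pooled AE comparisons be called the only formal safety tests, since section 2.10 can be read as covering each AE type.

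Three further points stand. No passage attributes muscular tremor to either drug, so the argument does not extend to it. The Discussion states the trial's safety expectation in terms of haemodynamic and respiratory depression, and those AEs are unaffected. The error works against fospropofol, so it could not create a false safety advantage for it through this item.

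None of this removes the contradiction over injection pain.

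**Conclusion.** The point holds for pain on injection. Section 2.6 attributes to the endoscopy an event that the Introduction and Discussion attribute to propofol, that can occur before the endoscopy begins, and that the Abstract classes as an adverse event. The probable consequence is that it is left out of the drug-related AE comparison, or graded no higher than possibly related, so that propofol's drug-related AE incidence is understated. For the total AE comparison the text is ambiguous.

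The size cannot be derived from the documents. The shift from 0 to between 5.6 and 38.5 points rests entirely on the assumed pain rates, the assumed 30% background and independence. The count of 13 to 51 patients is an upper figure under an assumed incidence, not an estimate of patients lost from the comparison.

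The primary outcome, the margin and the sample size are untouched. The sentence should still be corrected, because the classification alone can create or remove a between-arm difference in a planned comparison.

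**What to change.** In section 2.6, take pain on injection out of the operational reactions. Record it as an AE, grade its causality by Table 2, and state that it enters both the AE and the drug-related AE comparisons of section 2.10. Also report it by arm as its own item. Reconcile section 2.6 with the Abstract so that both give the event the same status. Muscular tremor need not be moved.

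The cost is a reworded sentence in section 2.6, a matching statement in section 2.10 and a small change to a CRF category. No new data are needed, because Table 1 already schedules the assessment. The change should be made before the events are classified for analysis.

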### 2.4 Study procedures

On the day of the gastrointestinal endoscopy, the patient will be given an intravenous infusion channel in the waiting room. After admission to the endoscopy room, all patients will be placed in a left lateral decubitus position and monitored according to our hospital standards including real-time monitoring of electrocardiogram (ECG), peripheral blood oxygen saturation (SpO_2_), end-tidal carbon dioxide (EtCO_2_), non-invasive blood pressure (NIBP), and respiratory rate (RespR) measured every 5 min. Supplemental oxygen will be given via a transparent nasal cannula at 5 L/min throughout the procedure.

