The patients will receive intravenous sedation regimen according to previous literature (Gan et al., 2010; Bergese et al., 2013), administered by the same anesthesiologist unaware of patient allocation group. All patients receive analgesic pre-treatment with sufentanil 5 μg via an intravenous infusion channel. It is recommended that patients receive only one additional dose of sufentanil 2.5 μg if the patient continues to experience pain during the procedure; however, additional doses of sufentanil (given at least 10 min after the previous dose) are allowed. After 2 min, an initial bolus dose of fospropofol 6.5 mg/kg or 1.5 mg/kg propofol and supplemental doses of fospropofol 1.6 mg/kg or 0.5 mg/kg propofol will be administered as needed to achieve a Modified Observer’s Assessment of Alertness/Sedation (MOAA/S) score ≤4 according to random group, allowing the physician to start the procedure. The bidirectional endoscopic procedures will be performed by experienced professional endoscopic teams in an esophagogastroduodenoscopy-colonoscopy sequence (Cao et al., 2017; Laoveeravat et al., 2020). This dosing schedule is also used to maintain adequate sedation levels during the procedure if the patient has a MOAA/S score ≥4 and shows purposeful movement. As deep levels of sedation (MOAA/S scores of 0 and 1) may be associated with an increased risk of respiratory compromise, additional doses of fospropofol or propofol are not administered to patients who had a MOAA/S score below four or who is not show purposeful movement during the sedation phase. If the patient sufferes from respiratory depression (SpO_2_ <90% for >10 s), the essential respiratory support such as chin/jaw lifting or assisted mask ventilation will be provided immediately until SpO_2_ returns to normal. In case of hypotension (MAP <70 mmHg or the decline reached 20% of the basal value) lasting more than 1 min, rehydration and intravenous injection of 50 µg phenylephrine will be administered. If bradycardia (HR < 50 beats/min) occurred, 0.5 mg atropine will be given intravenously.

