### 2.7 Data collection

Demographic data [including age, sex, race, height, weight, and body mass index (BMI)] and baseline characteristics (including comorbidities, preoperative medications, baseline MAP and HR values, and ASA status) will be collected prior to the procedures. The primary and secondary outcome measures and other perioperative data will be documented by a trained independent investigator blinded to group assignment. All raw data will be recorded on the Case Report Forms. The lead investigator will be responsible for the completeness and accuracy of data.

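### Section 2.4 requires treatment before section 2.6 counts the event, so hypoxia, hypotension and bradycardia corrected in that gap drop out of the safety comparison

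*Protocol article*

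**What the plan says.** Section 2.4 of the protocol article sets the treatment triggers and section 2.6 defines the events.

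- **Oxygen saturation.** Under 2.4, in "respiratory depression (SpO_2_ <90% for >10 s), the essential respiratory support such as chin/jaw lifting or assisted mask ventilation will be provided immediately". Under 2.6, "Hypoxia is defined as pulse oxygen saturation (SpO_2_) < 90% lasting for >30 s".
- **Blood pressure.** The 2.4 trigger for fluids and phenylephrine reads "In case of hypotension (MAP <70 mmHg or the decline reached 20% of the basal value) lasting more than 1 min". Under 2.6, "hypotension is defined as systolic blood pressure (SBP) < 90 mmHg or a decrease of 20% from baseline lasting for >2 min".
- **Heart rate.** Under 2.4, "If bradycardia (HR < 50 beats/min) occurred, 0.5 mg atropine will be given intravenously". Under 2.6, "bradycardia is defined as heart rate (HR) < 50 beats/min and lasting for >2 min".

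The monitoring list in 2.4 ends with "non-invasive blood pressure (NIBP), and respiratory rate (RespR) measured every 5 min". Section 2.7 lists "baseline MAP and HR values" among the baseline data and does not mention baseline SBP. Section 2.10 compares adverse event incidence between arms by a chi-square or Fisher's exact test. The Discussion expects fewer haemodynamic and respiratory depression events with fospropofol.

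**The concern.** Treating earlier than one counts is sound care and not in itself an error. Here, however, the required treatment can end the episode before it qualifies as an event, and nothing in 2.5, 2.6 or Table 1 says that a treated episode counts anyway. A patient who desaturates, receives mask ventilation just after 10 s and recovers at 25 s has no defined hypoxia event.

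These are the events on which the Discussion expects fospropofol to do better. A definition tied to episodes that outlast the protocol's own rescue leaves fewer events in both arms. A null result could then be read as similar respiratory and haemodynamic safety when the comparison had little chance of showing a difference.

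**Working it through.** **1. The two rules side by side**

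| Sign | Treat (2.4) | Count (2.6) | Gap |
|---|---|---|---|
| SpO2 <90% | >10 s | >30 s | 30 − 10 = 20 s |
| Hypotension | MAP <70 mmHg or 20% fall, >1 min | SBP <90 mmHg or 20% decrease, >2 min | 120 − 60 = 60 s |
| HR <50 | no duration stated | >2 min | up to 120 s |

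Treatment comes first for all three signs. Only episodes that end inside the gap are lost.

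**2. Hypotension: which pressure?** The absolute cut-offs name different pressures. Neither section names the pressure for the 20% fall. With MAP = (SBP + 2 × DBP)/3, take a fall from 125/70 to 105/50:

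- MAP before: (125 + 140)/3 = 88.3. MAP after: (105 + 100)/3 = 68.3. Change −22.6%, so the episode is treated.
- SBP: 105 is not below 90, and the change is (105 − 125)/125 = −16.0%.

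If the 20% in 2.6 means SBP, this episode does not count however long it lasts. If it means MAP, it counts once it exceeds 2 min.

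**3. Hypotension: can the durations be seen?** If the 5-min interval in 2.4 applies to NIBP, an episode of 2 min coincides with a scheduled reading with probability 2/5 = 40%, and two successive low scheduled readings span 5 min. Scheduled readings alone then cannot establish 1 min or 2 min.

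**4. Possible effect on the comparison.** The article does not give the share *f* of treated episodes that reach the counting time, so a range is shown with the same *f* in both arms. Inputs:

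- 128 per arm (sections 2.2 and 2.9).
- 30% under propofol. The Discussion gives about this figure for desaturation and hypotension events in earlier studies; using it as the rate of reaching the 2.4 trigger is an assumption.
- A halving to 15% under fospropofol, and a second scenario of 20% v 10%. Both are assumptions.

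The counted rates are p1·f and p2·f, with d their difference and p̄ their mean. Power = Φ[(d − 1.96·SE0)/SE1], where SE0 = √(p̄(1 − p̄)·2/128) and SE1 = √([p1f(1 − p1f) + p2f(1 − p2f)]/128).

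- f = 1, 30% v 15%: SE0 = 0.0522, SE1 = 0.0513; (0.15 − 0.1023)/0.0513 = 0.93; power 82%.
- f = 0.5, 15% v 7.5%: SE0 = 0.0395, SE1 = 0.0392; (0.075 − 0.0774)/0.0392 = −0.06; power 48%.

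| Share counted, *f* | Patients counted, 30% v 15% | Power, 30% v 15% | Power, 20% v 10% |
|---|---|---|---|
| 100% | 38.4 v 19.2 | 82% | 61% |
| 90% | 34.6 v 17.3 | 77% | 56% |
| 80% | 30.7 v 15.4 | 71% | 50% |
| 50% | 19.2 v 9.6 | 48% | 33% |
| 25% | 9.6 v 4.8 | 25% | 18% |

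Treated but uncounted patients at 30% v 15%: 128 × (0.30 + 0.15) × (1 − f), which is 5.8 at f = 0.9 and 28.8 at f = 0.5.

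**5. What is untouched.** The sample size in 2.9 rests on the success rate, not on these events. It reproduces: 2 × 0.95 × 0.05 × (1.960 + 0.842)²/0.08² = 116.5, so 117 per arm and 234 in total.

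**The case against.** The case for leaving the definitions alone has several parts.

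- **Not every treated episode is lost.** A reader might infer that any episode corrected by treatment falls outside the definitions. The text does not support that: a treated episode that still exceeds 30 s or 2 min counts. That HR <50 is treated at once is likewise an inference from the missing duration.
- **The hypotension wording is open.** A reader might infer that a treated low-MAP episode never counts. The 125/70 example needs the 20% to mean SBP. Baseline MAP in 2.7 makes a MAP reading plausible, and the 2-min condition may attach only to the 20% fall, in which case SBP below 90 would count without delay. These doubts stand, but they are themselves a reason to name the pressure. The mismatch of absolute cut-offs and the hypoxia and bradycardia gaps do not depend on them.
- **The 5-min interval may apply only to respiratory rate.** If it does apply to NIBP, the 1-min v 2-min gap has little practical meaning, so the two arguments should not be added together. A 1-min persistence rule also implies some unscheduled readings. Both points stand.
- **Brief events may be recorded elsewhere.** The abstract lists desaturation and hypotension tiers without durations, Table 1 gives no durations, the list in 2.6 is open-ended, and the case report form, which is not shown, may record rescue. For that reason the absence of rescue as an outcome is not the finding. None of this alters the explicit definitions in 2.6.
- **Duration limits screen out artefact.** True, and worth preserving as a separate tier.
- **The effect may be small.** If 90% of treated episodes count, power moves only from 82% to 77%. The rates and shares are assumed, and one *f* is used for three different gaps.

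**Conclusion.** The point holds in limited form and is worth correcting. Followed as written, 2.4 and 2.6 undercount respiratory and haemodynamic events by the number of episodes that treatment ends within 20 s, 60 s or up to 120 s of the trigger. The size is unknown: modest if most treated episodes outlast the gap, large if rescue usually works quickly. The power figures illustrate this under assumed rates and an equal counted share in both arms; they are not estimates for this trial.

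A reader might infer bias in favour of one arm. The documents do not support that: the treating anesthesiologist and outcome observers are blinded and one rescue rule applies to everyone, so the loss is probably similar in both arms and unequal loss is only a possibility. The trial is not powered for safety, and at 20% v 10% power is only 61% even when every treated episode counts. The primary outcome, sample size and non-inferiority conclusion are unaffected.

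**What to change.** 1. In 2.6, also count as an event any episode that meets the 2.4 trigger and receives the protocol treatment: airway support for SpO2 <90% for >10 s, phenylephrine for hypotension, atropine for HR <50. A precautionary jaw lift at SpO2 of 90% or more does not count.
2. Keep the >30 s and >2 min definitions as a sustained-event tier.
3. Report airway support, phenylephrine and atropine use by arm.
4. Name one pressure for treating and counting, including for the 20% fall; MAP fits the baseline data in 2.7. For the added event in item 1, define hypotension by a reading below threshold or by treatment given, not by minutes.
5. Align the abstract's desaturation and hypotension terms with 2.6. The tests in 2.10 can stay.

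The cost is a few lines in 2.4 and 2.6, and up to three tick-boxes if the case report form lacks them. No extra patients or scheduled measurements are needed. The downside is that more brief or artefactual episodes will be counted; the sustained tier offsets this and keeps comparability with other studies.
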